#### Conventional RAGT

Subjects allocated to this group will receive gait rehabilitation on the Lokomat device (Hocoma AG, Volketswil, Switzerland) as the previous treatment group. In this case, the parameters for setting up the machine will be determined by the physiotherapist administering the patient’s specific characteristics. The effective treatment duration will be 30 min, considering a preparation time for the patient on the machine of approximately 30 min.

#### Overground training

Subjects allocated to this group will receive a 1-hour walking training session supervised by a physiotherapist. During this time, the subject will perform a 40 min walk on a flat surface, preceded by a warm-up phase and a 10 min warm-down phase each. Subjects will walk back and forth approximately 30 m using their walking aid. If necessary, patients will benefit from recovery breaks, followed by resumption of exercise.

At the end of the treatment, the total distance walked, as well as the effective walking time, will be recorded on a special form.

### Concomitant care and recommendations

All patients receiving treatment will be asked to avoid other simultaneous physiotherapy treatments for the duration of the study until follow-up.

### Fidelity to treatment and adverse events monitoring

To guarantee that an experienced research group member will train in the most accurate intervention, the physiotherapists involved in using the Lokomat and conventional gait will be tested, and their abilities will be tested.

At the beginning of the study, each physiotherapist will be provided with a form for recording the intervention specifications. Any unpredictable adverse event will be recorded in each patient’s registry and the study’s electronic database and managed according to the hospital’s policies, with referral for appropriate medical follow-up.

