## Abstract

Gait disorders are the most frequent symptoms associated to multiple sclerosis (MS). Robot-assisted gait training (RAGT) in people with MS (PwMS) has been proposed as a possible effective treatment option for severe motor disability without significant superiority when compared to intensive overground gait training (OGT). Furthermore, RAGT at high intensity may enhance fatigue and spasticity. This study aims to evaluate the effects of a low-intensity RAGT at progressively increasing intensity compared to conventional RAGT and OGT in PwMS and moderate to severe walking impairment. 24 PwMS will be recruited and assigned to one of the three treatment groups: low-intensity RAGT at progressively increasing intensity, conventional RAGT and OGT. All participants will receive 3-weekly treatment sessions of 3 hours each for 4 weeks. In the first 2 hours of treatment, all participants will receive a rehabilitation programme based on stretching exercises, muscle strengthening and educational interventions. During the last hour, subjects will undergo specific gait training according to the assignment group. Outcomes will be assessed before and after treatment and at 3-month follow-up. The primary outcome is walking speed. Secondary outcomes include mobility and balance, psychological measures, muscle oxygen consumption, electrical and haemodynamic brain activity, urinary biomarkers, usability, and acceptability of robotic devices for motor rehabilitation. The results of this study will provide a safe, affordable and non-operator-dependent, intervention for PwMS. Results in terms of functional, psychological, neurophysiological and biological outcomes will confirm our hypothesis. The study’s trial registration number: NCT06381440.

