### Outcome assessment and data collection

The same physiotherapist will record all outcome measures at the Operative Unit of Physical and Rehabilitation Medicine of Ferrara University Hospital, blinded to the randomisation list. Clinical and instrumental evaluation will be performed before (T0) and after (T1) the twelve sessions of treatment and at 3-month follow-up (T2).

A clinical psychologist with expertise in MS from the Department of Neuroscience, Biomedicine and Movement Sciences at the University of Verona will remotely assess the robot technology’s usability, acceptability and perceived pleasantness. The assessor will be blinded to the patient allocation group, and the evaluation will be performed only at T1.

A team member will record each participant’s general demographic information, including age and gender, as well as their comorbidities and medical history (table 1).

**Table 1 T1:** Schedule of enrolment, interventions and assessment

Time point	Study period				
	Enrolment	Allocation	Postallocation		Close-out
	T-1		T0	T1	T2
Enrolment					
Eligibility screen	X				
Informed consent	X				
Allocation		X			
Interventions					
Low-intensity RAGT at progressively increasing intensity					
Conventional RAGT assessments					
OGT					
Primary outcome					
T25-FW			X	X	X
Secondary outcome					
Clinical measures and questionnaires			X	X	X
Psychological assessment			X	X	X
Haemodynamic and metabolic evaluations			X	X	X
Electrical brain activity			X	X	X
Laboratory-based measures			X	X	
Acceptability of robot intervention				X	

OGT, overground training; RAGT, robot-assisted gait training; T0, before treatment; T-1, enrolment time; T1, post-treatment; T2, 3 months follow-up; T25-FW, Timed 25-Foot Walk test.

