#### Clinical measures and questionnaires

Timed Up and Go test: A reliable measure of functional mobility.^33^ The task requires the patient to stand up from a chair, walk 3 m, cross a marked line on the floor, turn around, walk back to the chair and sit down. The time taken to complete the task is recorded using a stopwatch.6 min Walk Test: A reliable measure of walking endurance.^34^ Subjects will be instructed to walk as quickly and safely as possible for 6 min, with the option to slow down and rest if necessary. The total distance walked will be recorded.Berg Balance Scale: A 5-point ordinal scale used to assess the ability to maintain balance statically and during functional movements,^35^ widely used in PwMS.^36^
Modified Ashworth Scale: A 6-point measure of spasticity performed at the flexor and extensor muscles of the hip, knee and ankle.^37^
Multiple Sclerosis Impact Scale-29: A questionnaire that evaluates the impact of MS on physical and psychological functioning. It comprises 29 items, with 20 items assessing physical activity and 9 assessing psychological state.^38^
Multiple Sclerosis Walking Scale-12: A questionnaire used to evaluate the impact of MS on walking ability. It comprises 12 items that inquire about the patient’s perception of gait speed, running, confidence in ascending/descending stairs, balance and fatigue.^39^
Fatigue Severity Scale: A short questionnaire that requires the subject to rate their level of fatigue from 1 to 7.^40^

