### Data monitoring and interim analysis

The study does not have a data monitoring committee. The research coordinator will conduct an interim analysis every 6 months to determine whether the study should be stopped, modified or continued. Any subsequent changes will be discussed by the research team and communicated to the funding agency and the ethics committee.

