## Discussion

This pilot randomised controlled trial aimed to investigate the efficacy of robot-assisted gait rehabilitation in PwMS by identifying the robotic intervention’s loading factors, related metabolic response and the patient’s perspective. Identifying these non-operator-dependent intervention models would optimise the use of RAGT in future research studies and clinical practice.

We expect this study to observe an improvement in gait, mobility and balance in all patients, both those who received robot-assisted gait rehabilitation and those who received OGT. However, considering the results of increasing training intensity in other populations,^16 19 23^ we expect significantly greater changes in subjects assigned to the low-intensity RAGT at progressively increasing intensity group than in the other treatment groups.

Identifying the optimal dose response could be useful in PwMS, where fatigue management must be considered when defining the rehabilitation intervention and its parameters. The novelty of the intervention we will apply lies in proposing a low-intensity intervention and gradually increasing its intensity throughout the treatment sessions. This approach seems in contrast to literature recommendations regarding exercise characteristics that must be intense and high doses to promote learning mechanisms and neuroplasticity.^57 58^ The idea that more is better may not be suitable for a patient in whom symptoms like fatigue and spasticity caused by high-intensity training may compromise the effectiveness and applicability of the intervention, particularly in patients with a high disability level. Furthermore, implementing a low-intensity protocol would broaden the range of PwMS who can benefit from robotic gait therapy.

Concerning exosomal urinary miRNAs, we expect to identify one or more miRNA correlated with MS to confirm that urine is a useful body fluid for detecting molecules related to this pathology. We also expect to be able to establish one or more miRNA panels to be used as diagnostic/prognostic biomarkers of the effects of treatments, regardless of the intervention.

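### The adverse event rule covers only unpredictable events, so foreseeable harms during treatment have no stated event record behind the Abstract's safety claim

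*Protocol article*

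**What the plan says.** The section Fidelity to treatment and adverse events monitoring gives the recording rule: "Any unpredictable adverse event will be recorded" in the patient's registry and the study database, with medical referral under hospital policy. No other section of the article provides for recording expected events.

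The article names harms that it does expect. The Abstract says that "RAGT at high intensity may enhance fatigue and spasticity". The Discussion adds that "symptoms like fatigue and spasticity caused by high-intensity training may compromise the effectiveness and applicability of the intervention". The Abstract also announces a conclusion: "The results of this study will provide a safe, affordable and non-operator-dependent, intervention for PwMS".

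Other provisions that bear on harm:

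- Two secondary outcomes address the named harms: "Fatigue Severity Scale: A short questionnaire that requires the subject to rate their level of fatigue from 1 to 7" and "Modified Ashworth Scale: A 6-point measure of spasticity performed at the flexor and extensor muscles of the hip, knee and ankle". Table 1 schedules them at T0, T1 and T2.
- Acceptability of robot intervention describes a questionnaire at T1 that includes safety and concerns the robotic intervention.
- Under Intervention, a patient who misses more than three of the 12 sessions is excluded from the study.
- Data monitoring and interim analysis says "The study does not have a data monitoring committee", and has the research coordinator review the study every 6 months.
- The limitations paragraph of the Discussion says that a pilot this small permits no definitive conclusion.

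**The concern.** A rule limited to unpredictable events leaves out those that could be predicted, and the article has predicted some in writing. The article gives no criterion for telling the two kinds apart, so similar events could be logged for one patient and not for another.

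At stake is how complete the harm data are over the 4 weeks of treatment. The case for a gentler schedule rests partly on harms expected from more intense training, and the Abstract promises safety as a result of this trial. A safety statement needs a count of what happened, whether or not someone could have foreseen it.

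**Working it through.** The article gives no figure to reproduce on this point. The sample of 24 is stated without a calculation. The check is a comparison of the recording routes, followed by a calculation for context.

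**Which harms does each route capture?**

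| Kind of harm | Adverse event record as worded | Fatigue and spasticity scales (T0, T1, T2) | T1 questionnaire |
|---|---|---|---|
| Unpredictable event, any arm | Yes | Not designed for it | Robot intervention only |
| Fatigue or spasticity still present at T1 or T2 | Not provided for | Yes, all arms | Robot intervention only |
| Fatigue or spasticity that arises in treatment and resolves before T1 | Not provided for | No measurement between T0 and T1 | Robot intervention only, from recall |
| Foreseeable harm with no outcome scale | Not provided for | No | Robot intervention only |
| Fatigue or spasticity in a patient excluded for missed sessions | Not provided for | Uncertain | Uncertain |

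The third and fourth rows are the gap: no stated event record, and no scale at the right time or for the right harm. A scale score also does not show when an event occurred, whether it was related to training, or how many events there were. The questionnaire does not fill the gap, because it is given once and concerns the robotic intervention, so it offers no comparison with overground training.

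In the last row, exclusion starts at 4 missed sessions, that is, at 12 − 4 = 8 attended or fewer. The Intention to treat section plans multiple imputation for missing data, but the article does not say whether excluded patients are still assessed. If they are not, a patient who stopped coming because of fatigue or spasticity would have an imputed T1 score and no event entry.

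**How much could complete recording show?** With zero events in n patients, the exact one-sided 95% upper limit on the true proportion affected is 1 − 0.05^(1/n).

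- One arm, n = 8: 1 − 0.05^(1/8) = 0.312, or 31%.
- Both robotic arms, n = 16: 1 − 0.05^(1/16) = 0.171, or 17%.
- All patients, n = 24: 1 − 0.05^(1/24) = 0.117, or 12%.

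The chance that an arm of 8 shows at least one affected patient is 1 − (1 − p)^8. For assumed true proportions p of 5%, 10% and 20% (the article gives none), this is 34%, 57% and 83%.

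These figures follow from the sample size and hold whatever the recording rule. They do not measure the effect of the qualifier. They show how little a safety claim could rest on even if every event were logged.

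**The case against.** The strongest reply is that the two harms the article names are among those it measures most carefully. A reader might infer from the recording rule that fatigue and spasticity drop out of the trial. They do not: both have a scale, taken in every arm at three time points by an assessor described as blinded, and the Statistical analysis section compares outcomes across the three groups. This stands, and it confines the point to the event record.

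Three other inferences are tempting and are not supported.

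- *The between-arm comparison of harms is biased toward no difference.* The article plans no between-arm comparison of adverse events. The planned comparison of fatigue and spasticity uses the scales, which the recording rule does not touch.
- *The 6-monthly review sees only a filtered list.* The article does not say what data that review uses.
- *The event count is zero by construction.* That could hold at most for events judged predictable. Unpredictable ones are still recorded.

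It is also fair to say that the qualifier may be loose wording for any event, that safety is not a listed aim, and that a journal article leaves much adverse event detail to the full protocol. The last argument does not remove the point. The article does not merely omit detail; it states a rule, and the rule as stated is too narrow. If any event was meant, the correction is one word.

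Finally, the Discussion calls robotic training safe and well tolerated in this population on the strength of a cited source. The Abstract, however, attributes the safe intervention to the results of this study.

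**Conclusion.** The point holds in a limited form. As worded, the rule does not provide for recording foreseeable adverse events. The gap covers transient fatigue or spasticity between T0 and T1, and foreseeable harms without a scale. It may be wider for patients excluded after more than three missed sessions. The Abstract's safety statement would rest on that incomplete record, and it is at odds with the Discussion's own limitation. Even a complete record with no events would not rule out true proportions up to 31% in one arm or 12% overall.

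This rests on two assumptions: that staff follow the sentence literally, and that no fuller rule in an unseen full protocol overrides it. The number of events that would be lost cannot be estimated from the article. The correction is worth making because it is cheap and improves the safety data. It does not call the primary outcome or the planned scale comparisons into question.

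**What to change.** 1. In the adverse event section, delete the word *unpredictable*, so that every adverse event, expected or not, is recorded by the same method in all three arms. The form that physiotherapists already receive for intervention details can carry the entry.
2. Report adverse events and patients affected by arm, beside the Fatigue Severity Scale and Modified Ashworth Scale results.
3. Make the same record available to the 6-monthly review.
4. State whether patients excluded for missed sessions are still assessed at T1 and T2, so that the reach of the scales is clear.
5. Soften the Abstract's safety sentence to match the pilot limitation in the Discussion, for instance by saying that the study will describe the adverse events observed.

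The cost is a one-word deletion, a few added sentences, slightly more form-filling and a longer adverse event table. No dose, schedule or treatment rule changes.

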### Outcome assessment and data collection

The same physiotherapist will record all outcome measures at the Operative Unit of Physical and Rehabilitation Medicine of Ferrara University Hospital, blinded to the randomisation list. Clinical and instrumental evaluation will be performed before (T0) and after (T1) the twelve sessions of treatment and at 3-month follow-up (T2).

A clinical psychologist with expertise in MS from the Department of Neuroscience, Biomedicine and Movement Sciences at the University of Verona will remotely assess the robot technology’s usability, acceptability and perceived pleasantness. The assessor will be blinded to the patient allocation group, and the evaluation will be performed only at T1.

A team member will record each participant’s general demographic information, including age and gender, as well as their comorbidities and medical history (table 1).

**Table 1 T1:** Schedule of enrolment, interventions and assessment

Time point	Study period				
	Enrolment	Allocation	Postallocation		Close-out
	T-1		T0	T1	T2
Enrolment					
Eligibility screen	X				
Informed consent	X				
Allocation		X			
Interventions					
Low-intensity RAGT at progressively increasing intensity					
Conventional RAGT assessments					
OGT					
Primary outcome					
T25-FW			X	X	X
Secondary outcome					
Clinical measures and questionnaires			X	X	X
Psychological assessment			X	X	X
Haemodynamic and metabolic evaluations			X	X	X
Electrical brain activity			X	X	X
Laboratory-based measures			X	X	
Acceptability of robot intervention				X	

OGT, overground training; RAGT, robot-assisted gait training; T0, before treatment; T-1, enrolment time; T1, post-treatment; T2, 3 months follow-up; T25-FW, Timed 25-Foot Walk test.

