### Intervention

All participants will receive 3-weekly treatment sessions of 3 hours each for 4 weeks and 12 sessions. Patients who miss more than three rehabilitation sessions will be excluded from the study.

In the first 2 hours of treatment, an experienced physiotherapist will propose a programme based on stretching exercises, muscle strengthening and educational interventions. According to the assignment group, subjects will undergo specific gait training during the last hour. The different kinds of walking treatment are graphically represented in figure 2. All interventions will be delivered at the Rehabilitation Clinic of the University Hospital of Ferrara.

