#### Acceptability of robot intervention

At T1, we will administer an ad hoc questionnaire with closed 1–10 Likert scale and open-ended questions to assess patients’ experience with the robot intervention. The questionnaire will specifically explore the robotic intervention’s usability, acceptability, perceived pleasantness and safety.

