### Statistical analysis

Descriptive statistics (mean and 95% CI) will be reported at T0, T1 and T2 for all the variables. The distribution of data at baseline will be tested using the Shapiro-Francia tests. The baseline comparison between the three groups will be performed using the χ^2^ test for categorical variables and one-way analysis of variance (ANOVA) or the Kruskal-Wallis test for continuous variables, as appropriate. The outcome comparison between the three groups will be performed using a one-way ANOVA or Kruskal-Wallis test according to sample distribution. The intragroup comparison between T0, T1 and T2 will be performed using a t-test for paired data or a Wilcoxon test, depending on the distribution. In case of imbalances at baseline between the groups, appropriate statistical correction analyses (eg, analysis of covariance) will be adopted. Patient perspectives on the acceptability and usability of the robot intervention will be analysed using descriptive analysis for quantitative and inductive content analysis for qualitative data.^56^

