Psychiatric comorbidities represent a challenge when treating patients with PwMS due to the high prevalence of these disorders and the limited evidence for the efficacy of pharmacological treatments.^59^ On the other hand, there is emerging evidence about the effectiveness of rehabilitation programmes on mood symptoms in MS patients.^60^ Consequently, we anticipate that participation in rehabilitation treatments will yield positive outcomes for all patients, irrespective of their group allocation. However, variations in the exercises’ content across the three groups, particularly in intensity, are expected to elicit distinct experiences, perceptions and emotional responses from the patients, contingent on the nature of their assigned intervention.

We assume that both quantitative and qualitative data on the usability and acceptability of the robotic intervention will provide valuable insights into the patient’s ‘lived experience’.^61^ Qualitatively exploring the unique perspectives of PwMS and severe gait disability and collecting their suggestions regarding possible barriers and strategies for participation might inform future intervention implementation.^62^ Since RAGT is safe and well tolerated by patients with MS,^63^ we expect patients to provide positive feedback on the robotic intervention.

Our study may have some limitations. First, the pilot nature of the study does not allow any definitive conclusions due to the low number of subjects recruited. Second, the absence of a follow-up evaluation of more than 3 months does not allow us to conclude the effectiveness of the low-intensity intervention at progressively increasing intensity over time.

If the pilot study’s findings confirm our hypothesis, a randomised trial on a larger group of subjects would allow us to confirm our results.

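### The robot acceptability questionnaire is given only at T1 and low attenders are excluded before then, so early stoppers go unasked on a plain reading and the ratings may be too favourable

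*Protocol article*

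**What the plan says.** The Aims of the study section makes patients' views of the technology a secondary aim. Under Acceptability of robot intervention, the instrument and its timing are given: "At T1, we will administer an ad hoc questionnaire with closed 1–10 Likert scale and open-ended questions to assess patients’ experience with the robot intervention". Its scope follows: "The questionnaire will specifically explore the robotic intervention’s usability, acceptability, perceived pleasantness and safety".

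Outcome assessment and data collection assigns this to a psychologist working remotely and closes the schedule: "The assessor will be blinded to the patient allocation group, and the evaluation will be performed only at T1". The same section defines T1 as the visit after the twelve sessions, and Table 1 has a single mark for acceptability, at T1.

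The Intervention section sets the course: "All participants will receive 3-weekly treatment sessions of 3 hours each for 4 weeks and 12 sessions". It adds, without reference to the reason for absence: "Patients who miss more than three rehabilitation sessions will be excluded from the study".

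Statistical analysis states: "Patient perspectives on the acceptability and usability of the robot intervention will be analysed using descriptive analysis for quantitative and inductive content analysis for qualitative" data. The Intention to treat section promises analysis by intention to treat, with multiple imputation for missing data. The Discussion says that "we expect patients to provide positive feedback on the robotic intervention", and that learning what hinders participation would help later implementation.

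**The concern.** Stopping early is a strong sign that a device may not suit a patient. Measuring acceptability after exposure is sensible in itself. The difficulty is the combination of three things: one measurement after the full course, removal of low attenders before it, and no described contact when someone stops. Together they tend to restrict the sample to patients who attended most of the course.

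Two things are at stake. The ratings could look favourable partly through selection, which matters because favourable feedback is what the Discussion expects. The open-ended answers could also miss the patients who know most about barriers, and the Discussion names barriers as something to be learned.

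The trial's own rationale makes intolerance plausible. The Abstract and Discussion say that high-intensity robot training may worsen fatigue and spasticity and that this could limit its applicability, especially at high disability. The trial enrols patients with an Expanded Disability Status Scale score of 6 to 7.

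**Working it through.** **Inputs from the Protocol article**
- Sessions: 3 per week × 4 weeks = 12 (Intervention). This agrees with the stated 12.
- Patients: 3 groups × 8 = 24 (Sample size calculation). This agrees with the stated 24. Exposed to the robot: 2 × 8 = 16.
- Exclusion: more than 3 sessions missed. The fewest sessions a retained patient can attend is 12 − 3 = 9.
- Dropout rate, expected ratings, acceptability threshold: none given.

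**Step 1. Who reaches the questionnaire.** A patient who stops by the end of week 2 has attended at most 6 sessions and will miss at least 6. That exceeds 3, so the patient is excluded before T1. A patient who attends 9 or more sessions and then stops has missed at most 3, is retained, and would be asked. The group left out is therefore those who attend 8 or fewer sessions, for whatever reason.

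**Step 2. Size of the selection effect (assumed scores).** Let *k* of the 16 be excluded, let retained patients average 8 out of 10, and let excluded patients have rated *s*, with *s* from 2 to 4. All 16 are taken to have had at least one robot session.

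Mean if everyone is asked = [(16 − k) × 8 + k × s] / 16

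Bias of the T1-only mean = 8 − that mean = k × (8 − s) / 16

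| k | Mean, s = 2 | Mean, s = 4 | Bias (s = 4 to s = 2) |
|---|---|---|---|
| 0 | 8.00 | 8.00 | 0 |
| 1 | 122/16 = 7.63 | 124/16 = 7.75 | 0.25 to 0.38 |
| 2 | 116/16 = 7.25 | 120/16 = 7.50 | 0.50 to 0.75 |
| 3 | 110/16 = 6.88 | 116/16 = 7.25 | 0.75 to 1.13 |
| 4 | 104/16 = 6.50 | 112/16 = 7.00 | 1.00 to 1.50 |

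**Step 3. How likely is any exclusion?** With an assumed exclusion probability *p* per robot patient, the chance of at least one among 16 is 1 − (1 − p)^16:
- p = 5%: 56% (expected number 0.8)
- p = 10%: 82% (1.6)
- p = 15%: 93% (2.4)
- p = 20%: 97% (3.2)

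These are exclusions for any reason, so they are an upper limit on exclusions due to intolerance.

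**Step 4. Does the missing-data plan repair it?** Not for this outcome. Open-ended answers cannot be imputed. Acceptability has no baseline value to inform an imputation model. If intolerance causes the missingness, the missingness probably depends on the unseen rating itself.

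**The case against.** The strongest reply is that the article nowhere says discontinuers go unasked. The schedule fixes a time point, and no meaningful rating exists before exposure. The intention-to-treat statement points towards keeping randomised patients; if they were followed to T1 despite low attendance, most of the concern would disappear. Withdrawal procedures may also sit in a fuller protocol.

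Part of this stands. That early stoppers are not asked is the plain reading of exclusion combined with a T1-only schedule; it is not stated in those words. The exclusion rule and the intention-to-treat statement conflict, and the article does not say which governs. The point is nevertheless more than a missing detail, because the article itself fixes both the single time point and the exclusion.

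Several stronger readings are tempting and not supported:
- A reader might infer that only patients who accept the robot are sampled. Missed sessions count for any reason, two of each session's three hours are not robot training, and a patient who turns against the robot after nine sessions is still asked.
- A reader might infer that a comparison of acceptability between the two robot groups is distorted. No such comparison is specified; the analysis is descriptive, with content analysis.
- A reader might treat the expected positive feedback as a hypothesis under test. It is an expectation voiced in the Discussion.

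There are also partial safeguards. Adverse events are recorded for each patient, and a participant flow diagram is planned. These can show harms and numbers lost, but they supply neither ratings nor the stoppers' own accounts.

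**Conclusion.** The concern holds in conditional form. As written, the plan tends to leave early stoppers out of a stated secondary aim. If any are excluded because they do not tolerate the robot, the reported ratings are likely to be too high. That direction is a reasonable inference; the size is not derivable from the documents. The range of 0.25 to 1.5 points rests wholly on the assumed mean of 8 among retained patients, ratings of 2 to 4 among those excluded, and 1 to 4 exclusions among 16.

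It would go too far to say that the acceptability result is biased, since with no intolerance-related exclusions this mechanism produces no bias. Nor does this point bear on the Timed 25-Foot Walk comparison. It concerns one descriptive secondary outcome in a 24-patient pilot that already disclaims definitive conclusions. It is worth correcting because the correction is cheap and the lost information cannot be reliably recovered at analysis.

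**What to change.** 1. In Outcome assessment and data collection, replace the T1-only timing with: at T1, or shortly after robot training is stopped if that is earlier, for every robot-group patient with at least one robot session. Align Acceptability of robot intervention and Table 1.
2. Reconcile the exclusion rule in Intervention with the Intention to treat section, so that low attenders remain in the study for this assessment. Without this, item 1 cannot be carried out under study procedures. It concerns data collection only and takes no position on when training should stop.
3. Report the number who stopped, the sessions they attended and their reasons beside the ratings. Use all exposed robot-group patients as the rating denominator, and count any who never had a robot session separately.

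The cost is a short amendment to these sections and a few additional interviews. The psychologist already assesses remotely, so no extra visit is needed. The reported ratings may turn out less favourable.
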